**Fig. 1 Fig1:**
[figure not shown]
Overview of clusters of midwifery practices. Midwifery practices from three regions will be randomly allocated to one of four steps. At each step, practices that received training cross over from the control condition (V-MIS/usual care) to the experimental condition (PROMISE)

We will train clusters of midwives and OB-GYNs, subsequently, at four regular intervals (‘steps’). At each step, practices that received training cross over from the control condition to the experimental condition. We will measure outcomes at baseline, at each of the four steps (2 months apart, step 1 starting 2 months after baseline) and 2 months after the last step.

This study has been registered in the Dutch Trial Registry (NTR 6305) and was exempt from medical ethics review by the Ethics Committee of the Erasmus Medical Centre in Rotterdam (MEC-2016-605).

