#### Primary outcome

Our primary outcome measure is change in percentage of smoking pregnant women with whom midwives (or OB-GYNs) discussed specific quit-smoking strategies. We use the self-reported data from the questionnaires filled out by the midwives and OB-GYNs for this. We will calculate this outcome measure by dividing the number of women with whom the professional discussed specific smoking cessation strategies by the total number of smoking women seen by the professional. This will result in a percentage at each time point for each individual professional. We expected that this percentage will increase over time in the total sample, as more professionals will use the PROMISE protocol and will be better able to support smoking clients.

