#### Statistical analyses

We will use a Generalised Linear Mixed Modelling analysis in SPSS 25+ or R 3.0+ to analyse sample-wide changes in our primary outcome over time. In stepped-wedge designed studies, data should be interpreted at population level [34]. This means that not individual changes, but sample-wide changes over time are used to test the effectiveness of the new protocol (similar to a repeated cross-sectional design). In our study, all care professionals fill out a questionnaire at each of the six time points. In this questionnaire, they indicate the number of smoking women they have seen in the past month and the number whom they provided detailed smoking cessation counselling.

We calculate the percentage of smoking women who received detailed counselling for each care professional at each of the six time points. As each care professional will attend one of four training sessions, all professionals switch from the usual care condition (control) to the experimental condition at one of those time points.

Using a Generalised Linear Mixed Modelling (GLMM) analysis, we will analyse whether professionals provided detailed counselling to a higher portion of their smoking clients after receiving the training than before. We will include the factors ‘cluster’ (i.e. practices) and ‘individual’ (i.e. midwife/OB-GYN) as random effects, and ‘step’ will be included as fixed (time) effect. The exact link function (e.g. nominal, binominal) for the model will be based on the outcome variable. We will conduct an intention-to-treat analysis to control for lost to follow-up. Only members of the research team will have access to the research data.

As we do not anticipate any adverse effects in any of the two intervention arms, we will not conduct any interim analyses to determine if the trial needs to be stopped.

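### If the monthly counts are fitted as binomial, the listed random effects leave month-to-month variation within a professional unmodelled, so the standard error of the training effect can be too small

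*Protocol article*

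**What the plan says.** All of this is in the protocol article, under Primary outcome and Statistical analyses.

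- **Data.** The outcome is self-reported: "We use the self-reported data from the questionnaires filled out by the midwives and OB-GYNs for this". At each wave "they indicate the number of smoking women they have seen in the past month and the number whom they provided detailed smoking cessation counselling". There are six waves: "all care professionals fill out a questionnaire at each of the six time points".
- **Summary.** The two counts are divided: "This will result in a percentage at each time point for each individual professional".
- **Model.** A generalised linear mixed model is planned: "We will include the factors ‘cluster’ (i.e. practices) and ‘individual’ (i.e. midwife/OB-GYN) as random effects". Time is a fixed effect shared by all professionals.
- **Distribution.** Not settled: "The exact link function (e.g. nominal, binominal) for the model will be based on the outcome variable".

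No random term for professional-by-wave, practice-by-wave or single record is mentioned.

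**The concern.** The plan collects a numerator and a denominator for each professional at each wave. Of the two distributions it names, only the binomial suits such data. With random intercepts for practice and professional only, that model treats the women in one monthly report as independent given the two intercepts. A report is one person's recollection of one month. Workload in that month, or the way the count is recalled, could plausibly move the whole figure up or down. A Gaussian model puts such movement in its residual. A binomial model fixes its variance from the mean and has no residual to estimate.

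The training effect is estimated largely from changes between waves, so unmodelled wave-level noise bears directly on the primary test. If the noise is there, the confidence interval is too narrow and an effect of PROMISE may be declared too easily. This is a different matter from practices drifting apart over time: it arises even if every practice's underlying rate is stable, and a practice-by-wave term would not absorb it.

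**Working it through.** **1. The plan's own figure.** The Sample size section gives 18 professionals per cluster (35% vs 60%, two-sided α 0.05, CV 0.3, power 0.80). The Hussey–Hughes variance is

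var = Iσ²(σ² + Tτ²) / {(IU − W)σ² + (U² + ITU − TW − IV)τ²}.

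Take I = 4 step-clusters, T = 5 periods, U = 10, W = V = 30, τ = 0.3 × 0.35 = 0.105, and σ² = [(0.35 × 0.65 + 0.60 × 0.40)/2]/18 = 0.23375/18 = 0.01299. Then var = 0.003538/0.4606 = 0.00768, SE = 0.0876, and power = Φ(0.25/0.0876 − 1.96) = 0.81. With 17 per cluster it is 0.79, so 18 is reproduced. The only variance components are between clusters and binomial; there is none for month-to-month variation.

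**2. Why the binomial model understates the variance.** The listed model is logit(p) = μ + time + θ·condition + practice + professional. Suppose each professional-by-wave record also carries a deviation with logit SD ω. To first order, the variance of a count from m women is m·p(1 − p)·[1 + (m − 1)·p(1 − p)·ω²]. The bracket is 1 when m = 1 and grows with m and ω. At p = 0.35 and ω = 0.5 it is 1 + 4 × 0.2275 × 0.25 = 1.23 for m = 5, and 1 + 9 × 0.2275 × 0.25 = 1.51 for m = 10. Caseload and ω therefore decide the size.

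**3. Inputs.**
- From the documents: 23 + 3 = 26 practices in three regions, four steps, six waves, 54 professionals, control rate 35%, two-sided 5%.
- Assumed: practice logit SD 0.4 (CV 0.3 at 35% gives about 0.105/0.2275 = 0.46), professional logit SD 0.6, Poisson caseload, monthly logit SD ω.
- Also assumed: a fixed condition effect, which the section implies but does not list, and practices counted as treated from the wave of their own step.
- Only caseload clue (Regions section): at least 250 low-SES smokers per region per year, so 3 × 250/54/12 = about 1.2 new women per professional per month. Women seen per month, of any SES and over repeated visits, may be more.
- Meaning of ω: around 35%, one SD either way is 30–41% (ω = 0.25), 25–47% (0.5) or 17–59% (1.0).

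**4. Rejection rate of the 5% test with no training effect** (binomial model as listed, 1,000 runs per cell, Monte Carlo SE about 0.7–1.3 points):

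| Women per month | ω = 0 | 0.25 | 0.5 | 0.75 | 1.0 |
|---|---|---|---|---|---|
| 1.2 | – | – | 5.8% | – | 6.0% |
| 3 | – | 4.6% | 6.5% | – | 10.7% |
| 5 | 4.5% | 5.5% | 7.2% | 8.9% | 13.0% |
| 8 | – | – | 9.0% | – | 17.7% |
| 10 | – | 6.2% | 9.2% | 16.4% | 20.5% |

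At ω = 1.0 the mean reported SE against the actual SD of the estimate is 0.197 vs 0.250 (5 women) and 0.142 vs 0.225 (10 women). As a check, 2{1 − Φ(1.96 × SE/SD)} gives 12% and 22%, in line with 13.0% and 20.5%.

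**5. Other components.** A second simulation used practice SD 0.45, professional SD 0.8, 2 or 4 professionals per practice, mean 4 or 8 women, and 600 runs per cell. It gave 3.8–6.2% at ω = 0, 5.5–8.3% at 0.5 and 11.0–18.8% at 1.0.

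**6. Alternatives at ω = 1.0.**
- Binomial plus a professional-by-wave random effect: 3.0% (5 women) and 4.0% (10 women), 300 runs each. Under the second set of components, with 2 professionals per practice: 4% (4 women) and 6% (8 women), 200 runs each.
- Gaussian mixed model of the percentages with the listed random effects: 4.3% (5 women) and 6.5% (10 women), 400 runs each.

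**The case against.** The strongest reply is that the plan does not commit to the binomial model. The distribution is left to follow the outcome variable, binomial is only an example, and both sections reduce the counts to one percentage per professional per wave. A Gaussian mixed model of that percentage has a residual that is exactly the professional-by-wave variation, and it held its level reasonably well. This stands, and it makes the point conditional.

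A reader might infer that the planned primary test has a known false-positive rate well above 5%. The documents do not support that. Neither the number of smoking women seen per professional per month nor any within-professional monthly variance is given. Every rate above 10% in the simulations needs a monthly SD of 0.75 or more, and SD 1.0 exceeds the professional spread assumed in either simulation. At SD 0.25, or at the caseload floor implied by the regional criterion, inflation is negligible. That monthly reports vary beyond binomial chance is plausible, but the text does not show it.

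It can also be said that an overdispersion term is analysis-plan detail and that the article condenses a fuller document. Only part of this stands. The article does state the random effects, and it names a distribution for which that list is insufficient if monthly variation exists. Naming two factors does not exclude a third, but nothing in the text points to one.

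**Conclusion.** The point holds conditionally. With a binomial family and only practice and professional intercepts, monthly variation within a professional is left out of the standard error. Under the assumptions in the working, the actual level of the 5% test runs from about 5% to about 20%: 5–6% at monthly SD 0.25 or about 1.2 women per month, 7–9% at SD 0.5 with 5–10 women, and 13–20% at SD 1.0 with 5–10 women. The documents do not fix where in that range this trial lies. With a Gaussian model of the percentages the problem largely disappears (about 4–6.5%). It is a modest weakness in the stated model, worth closing because the remedy is cheap and concerns the only hypothesis test the article states.

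**What to change.** In the Statistical analyses section, add that if the counts are modelled as binomial events out of trials, the mixed model also includes a random effect for each professional-by-wave record, or uses a beta-binomial response, with the practice and professional intercepts kept.

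The cost is one sentence and one variance term. Confidence intervals become wider when the variation is present: at monthly SD 1.0 the mean SE rose from 0.197 to 0.273 (5 women) and from 0.142 to 0.242 (10 women), against actual SDs of 0.240 and 0.232 under the extended model. The extended model can thus be slightly conservative at low caseload. Its cost when no such variation exists was not simulated; little change would be expected.

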## Discussion

This article describes the study protocol for testing the effectiveness of the PROMISE smoking cessation counselling protocol for midwives and OB-GYNs. The PROMISE protocol is an adapted version of the existing V-MIS protocol and focusses on effective communication towards pregnant women with low SES or poor functional health literacy skills. Using a stepped-wedge randomised controlled design, we will evaluate the effectiveness of the PROMISE protocol while we implement it in 23 midwifery practices and three obstetrics hospital departments across three regions in the Netherlands. Over the course of the training period, we will assess the rate at which midwives and OB-GYN discuss smoking cessation strategies with smoking clients.

This study will be the first to introduce both carbon monoxide and storyboard leaflets for smoking cessation at a large scale among obstetrics care professionals. Both professionals and their clients will be unfamiliar with these materials. Although implementing the new protocol may be challenging at times, this study will deliver valuable insights into the added value of using these new materials and protocol in the Dutch context.

While midwives and OB-GYNs are the main study population of this project, we will develop extensive materials for post-natal care nurses and youth health care professionals too. By involving all obstetrics care professionals, we will create a systematic and comprehensive protocol for multidisciplinary smoking cessation support for pregnant women and young mothers. By motivating all care professionals to use similar communication techniques, support materials, and transferral documents, we might help reducing exposure to tobacco smoke among new-borns. Unfortunately, we will be unable to properly assess the level cooperation between professionals in this study. Future research might study ways of improving cooperation between all partners in local obstetric partnerships.

The results of this study will be submitted to an international peer-reviewed journal. If effective, the PROMISE protocol can be incorporated in the existing smoking cessation support protocols for pregnant women in the Netherlands. This will in turn motivate obstetrics care professionals throughout the Netherlands to provide smoking cessation support more frequently and help improving the health of mothers and their children.

## Data Availability

Not applicable.

## Abbreviations

CO: Carbon monoxide
OB-GYN: Obstetrics and gynaecology doctor
PROMISE: PROtocol for growing up smokefree using a Minimal smoking cessation Intervention Strategy in the Early stages of life
RCT: Randomised controlled trial
SES: Socioeconomic status
V-MIS: Minimal Intervention Strategy for Midwives (Dutch: Verloskundige Minimale Interventiestrategie)
